## Abstract

**Background:**

Adolescent refugees are particularly vulnerable to mental health problems, as they experience many risk factors associated with their resettlement at crucial stages of their physical and emotional development. However, despite having a greater healthcare needs than others, they face significant barriers to accessing healthcare services. Therefore, this study aims to test the effectiveness of a low-threshold, culturally adapted version of the skills training START NOW – START NOW Adapted - in reducing mental health problems among adolescent refugees.

**Methods:**

We will recruit 80 adolescent refugees (15–18 years) with symptoms of anxiety and depression or high perceived stress in Northwestern Switzerland. They will be randomly assigned to one of two study groups: an intervention group, receiving START NOW Adapted, and a control group, receiving treatment as usual (TAU). The intervention will last 10 weeks and will consist of one-hour sessions per week provided by a trained facilitator with the same cultural background, in the respective language. Assessments to collect depressive and anxious symptoms, perceived stress, social-ecological resilience, and emotion recognition abilities will be conducted pre-intervention, post-intervention (11 weeks later) and at the 3-month follow-up. Multilevel models will be computed with primary and secondary outcome measures as dependent variables. An effect of at least moderate size will be considered clinically relevant.

**Discussion:**

This randomized controlled trial aims to investigate the effectiveness of a culturally adapted version of START NOW, providing valuable insights to improve current health promotion for adolescent refugees in Switzerland (or rather lack thereof). Ultimately, the effects of START NOW may facilitate integration and promote healthy development while decreasing costs associated with treating migration- or conflict-related trauma.

**Clinical trial registration**: ClinicalTrials.gov, identifier: NCT06324864.

## Background

1

Over the last few decades, Europe has experienced one of the largest increases in international migration, which has contributed to making migration a major social, political and public health challenge (1). The increased migration rates result from a combination of natural and man-made disasters, including social, economic, and political instability (1). As these disasters cannot be expected to decrease in the future, it is essential to establish optimal healthcare for migrants, especially refugees (2).

Refugees are a subset of migrants who differ in the reasons for their displacement, namely a well-founded fear of persecution, conflict, violence or other forms of danger (3). Children and adolescents below 18 years of age make up about half of the worldwide refugee population (4). Due to several risk factors for their psychological well-being, refugees have higher prevalence rates of depression, PTSD and other anxiety disorders compared to the host-country population (5, 6). Several systematic reviews have found prevalence rates of up to 40% for self-reported depression, 37% for self-reported PTSD, and 42% for self-reported anxiety (7, 8). Adolescent refugees are particularly vulnerable to mental health problems because they experience many of the risk factors associated with their resettlement at crucial stages of their physical and emotional development (9).

Risk factors for adolescent refugees’ psychological well-being can be categorized into pre-, peri- and post-migration stressors (10). They can also be conceptualized at different levels according to Bronfenbrenner’s socio-ecological perspective, whereby youth development takes place in a complex interplay of different levels (e.g., individual, family, school, community, and society) (11). At the individual level, exposure to traumatic events before migration is associated with higher levels of depression, PTSD, and anxiety, especially if these traumatic events involve severe interpersonal violence (12). Pre-migration trauma even persists to impact refugees’ mental health years after displacement (5). At the family level, refugees who experience separation from family members peri-migration show higher levels of PTSD and emotional problems (12). Post-migration, decreased family functioning correlates with more internalizing and externalizing issues (13). At the community level, lower social support post-migration increases the risk of depression, PTSD, and anxiety (14). At the society level, experiences of discrimination as well as staying in settings with lower supervision post-migration predicts symptoms of depression, PTSD, and anxiety (12).

However, despite having greater healthcare needs than others, adolescent refugees encounter significant barriers to accessing healthcare services (15, 16). Systemic barriers include the lack of healthcare services and long waiting lists (16). Even if refugees are given a place in the healthcare system, a financial barrier is the affordability thereof, including payment for treatment, transport and medication (17). Understanding the complex healthcare system and the lack of information about it is also a barrier for many refugees (15). Another barrier, particularly among young asylum seekers, is mistrust of the healthcare system and the fear that health information could play a role in the asylum procedure (15). Refugees also often face challenges due to language difficulties and the scarcity of accessible interpreters who are both professional and culturally sensitive (15, 16). To overcome these barriers, peer approaches would be necessary, in which a certain basis of trust and understanding already exists due to a common cultural background. These peers could interact with refugees in a manner that respects cultural norms and values, aiming to support their healing and resilience (18).

## Objectives

2

To date, there is a significant lack of randomized controlled trials investigating the effectiveness of culturally adapted interventions for adolescent refugees provided by a trained facilitator with the same cultural background (19). Therefore, the primary aim of this RCT is to evaluate the effectiveness of a culturally adapted version of the group training START NOW in reducing mental health problems of adolescent refugees.

### Endpoints

2.1

Symptoms of depression and anxiety will be the primary endpoints because of their high self-reported prevalence of up to 42% in refugee populations and therefore their high relevance to participants (7, 8). The intervention START NOW also aims to improve emotion regulation, mindfulness and interpersonal effectiveness, which are effective skills in decreasing symptoms of depression and anxiety (20–22).

Secondary endpoints include perceived stress, social-ecological resilience, and facial emotion recognition.

We chose perceived stress as a secondary endpoint because of the many pre-, peri- and post-migration stressors that are risk factors for refugees’ mental health. These risk factors could be better managed since the intervention START NOW aims at improving distress tolerance (22). Adding to that, perceived stress has been found to mediate effects of protective resilience factors such as self-esteem on depression (23).

We included social-ecological resilience as another secondary endpoint because it has often been used to assess the effectiveness of interventions in pre-post and longitudinal designs (e.g., (24)).

We chose the secondary endpoint of facial emotion recognition (ER) because performance on measures of emotion recognition is a first step in emotion regulation (25). Consistent with the content and goals of CBTs, certain types of biases in ER that are associated with depressive symptoms, such as labeling emotionally neutral stimuli as negatively valenced, can be reduced following the START NOW intervention (26, 27).

### Hypotheses

2.2

Based on our primary and secondary endpoints, we have formulated the following hypotheses.

START NOW Adapted will be more effective than TAU in reducing symptoms of depression and anxiety, as assessed by the Hopkins Symptom Checklist (HSCL-25).START NOW Adapted will be more effective than TAU in reducing perceived stress, as assessed by the Perceived Stress Scale (PSS-10).START NOW Adapted will be more effective than TAU in increasing social-ecological resilience, as assessed by the Child and Youth Resilience Measure (CYRM-R).START NOW Adapted will be more effective than TAU in increasing facial emotion recognition, as assessed by the Penn Emotion Recognition Task (ER-40).

Additionally, besides investigating the intervention’s effectiveness, we aim to examine potential mediators to uncover the mechanisms of action (28). Specifically, we hypothesize:

The relationship between the group condition and changes in depressive and anxious symptoms (HSCL-25) is mediated by stress reduction (PSS-10).The relationship between the group condition and changes in depressive and anxious symptoms (HSCL-25) is mediated by increased resilience (CYRM-R).The relationship between increased resilience (CYRM-R) and changes in depressive and anxious symptoms (HSCL-25) is mediated by stress reduction (PSS-10).

## Methods

3

The protocol for this RCT was designed according to the Recommendations for Interventional Trials (SPIRIT; (29)) and was registered in the ClinicalTrials.gov trial database on March 21, 2024 (Trial registration number: NCT06324864). We will adhere to the guidelines outlined in the Consolidated Standards of Reporting Trials (CONSORT; (30)).

### Study design

3.1

The study is a confirmatory, randomized controlled trial with two arms that takes place in a monocentric, national setting and assesses effectiveness.

To evaluate feasibility, qualitative semi-structured interviews will be conducted with specialists working with refugees prior to the intervention study. These interviews will follow an inductive and explorative approach and involve staff from institutions such as asylum centers and dormitories for unaccompanied minors. To estimate the feasibility and effectiveness of this trial, specialists will be interviewed about their daily challenges, language and cultural barriers, as well as potential difficulties with the implementation and adaptation of START NOW. The inclusion of qualitative information can help to better understand how a complex intervention such as START NOW can work and aid in the adaptation process of the intervention (31).

After the conduction of these interviews, possible participants taking part in the intervention study are screened for eligibility. For those who are eligible, the study duration will be 6 months, including three assessments (shown in Figure 1): a baseline assessment (t1), a post-treatment assessment (t2), and a 12-weeks follow-up assessment (t3). In case a participant has missed a session, they will be marked as absent and the number of sessions will be taken into consideration in the data analysis. To minimize bias, participants will be randomly assigned to one of two experimental group conditions, (1) group skills training using an adapted version of START NOW, (2) TAU. Randomization should take place within 2 weeks before the intervention, after the baseline assessment (t1) has been conducted. Between t1 and t2, the intervention phase takes place over a period of 10 weeks, with one session per week for each group. The study takes place in a group setting since conducting mental health interventions via group workshops, which aim to enhance social interaction was observed to have a positive impact on participants’ mental health (19). For ethical reasons and to increase study-related commitment, participants in the control group (receiving TAU) as well as non-eligible participants will be offered the chance to receive treatment after the study concludes.

**Figure 1 fig1:**
[figure not shown]
Study Flow

### Study procedure

3.2

The overall study duration will be 2 years, starting in March 2024 with recruitment and ending in March 2026. In collaboration with the Department of Economic, Social and Environmental Affairs of Basel-Stadt, the study team will recruit participants from social welfare, migration + integration and inpatient counseling facilities, such as residential homes for unaccompanied minors, as well as associated organizations such as the Center for Social Pedagogy and Psychotherapy in Basel. At this point, institutions will also be asked if some of their staff are willing to participate in qualitative semi-structured feasibility interviews before the start of the intervention study. In addition, we will contact associated networks for young people with a migration background, such as leisure activities or clubs and other institutions in Basel-Land. The relevant institutions and networks will be informed about the study by email or by telephone. Interested institutions will be given flyers and interested young people will be referred to our team.

On site or during a video call, the investigators (study team members) will explain to each participant the nature of the study, its purpose, the procedures involved, the expected duration, the potential risks and benefits, and any inconvenience that may be involved. Each participant will be informed that participation in the study is voluntary, that he or she may withdraw from the study at any time, and that withdrawal of consent will not affect subsequent medical care and treatment. If necessary, a translator (professional translator or bilingual native speaker from the institution staff) will also be present. All participants in the study will receive a participant information sheet and a consent form describing the study and providing sufficient information in the native language of the participants so they can make an informed decision about their participation in the study. The participant will be given 1 week to decide whether to participate. The formal consent of a participant, using the approved consent form, will be obtained before the participant is submitted to any study procedure. The consent form will be signed by the participant, sent with a prepaid envelope and dated upon arrival by the investigator or his designee. The date of receipt of the consent form is the date of inclusion for participation in the study. A copy of the signed informed consent will be given to the study participant. The consent form will be retained as part of the study records. The informed consent process will be documented and any discrepancies in the process described in the protocol will be explained.

After informed consent has been given, participants will be screened for eligibility. Any participants can withdraw from the study at any time without personal disadvantages and without having to give a reason. The applicants can also decide about termination of treatment in case of protocol violations or if the applicants believe continuation in the study would be detrimental to the participants` well-being. If participants withdraw their participation prior to randomization, other eligible individuals can move up. Premature withdrawals in the group training will not be replaced after the beginning of the intervention. Relevant additional treatments (e.g., individual psychotherapy) administered to the participant upon entry to the trial or at any time during trial participation are regarded as concomitant treatments and will be documented as well as concomitant medication.

After the screening process, eligible persons will be notified by the project management through their institution about their participation opportunity. If someone is not eligible, both the institution as well as the individual will be notified online via mail. If eligible participants still wish to take part, they are randomly assigned to a group. In general, randomization will be done within each institution by randomly assigning participants to either the intervention or control group using computer algorithms. If not enough adolescents within an institution wish to participate, we will make an adjustment to the general randomization process by creating cross-institutional groups. Participants will be randomized in separate steps for each gender group. In this way, we ensure a random distribution between the intervention and control groups within each gender group and a safe environment for all participants. This is in tune with cultural norms and expectations of the target population, and this way, our results are more likely to provide important insights around cultural idioms of distress that may be gender specific (32).

### Eligibility criteria

3.3

The study population consists of adolescent refugees between the ages of 15 and 18 who are temporarily or permanently resettled in Switzerland and have given informed consent. In November 2023, the majority of new arrivals to the asylum procedure in Switzerland were from the following countries: Ukraine, Turkey, Afghanistan and Algeria (33). For this reason, our participants will presumably consist of homogeneous groups from these nations, as groups with the same migration background show greater intervention effectiveness than groups with different migration backgrounds (34).

The design of our study has been developed considering the conditions of regular clinical practice and focusing on outcomes crucial for making clinical decisions. In this context, the eligibility criteria enable the source population to represent diverse characteristics of external populations, accounting for comorbidities and varying compliance rates (35).

According to this study population, study inclusion criteria include:

Being a refugee resettled in Switzerland temporarily or permanentlyAged between 15 and 18Able to speak, read and understand one of the following languages: German, English, Turkish, Persian, Ukrainian, ArabicAble to give informed consent as documented by signatureAt least sub-clinical depressive symptoms assessed by the Hopkins Symptom Checklist-25 (HSCL-25); total score > 1.75 (36), orHaving elevated levels of psychological distress assessed by Kessler Psychological Distress Scale (K10); total score > 20 (37)

Study exclusion criteria include:

Suicidality assessed by the Suicide Behaviors Questionnaire-Revised (SBQ-R); total score > 6 (38)Planning to leave Switzerland in the next 6 monthsConcurrent CBT-based skills training similar to START NOW

We included underage participants since there is a lack of culturally adapted, low-threshold interventions targeting this demographic, notwithstanding the fact that approximately 50 % of all psychiatric disorders manifest in individuals at the age of 14 (39). Symptoms showing that a participant is unwilling to participate in the study will result in the participant being excluded from participation.

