#### Screening measures

3.5.1

Screening measures include demographics such as age or country of origin, inclusion criteria including the HSCL-25 and the K10, exclusion criteria including the SBQ-R, and the World Health Organization Well-Being Index (WHO-5).

The K10 is a 10-item self-report questionnaire aimed at assessing overall distress levels. It gathers information on anxiety and depressive symptoms experienced by an individual within the past 4 weeks. Participants answer on a 5-point Likert Scale (1 = none of the time, 5 = all of the time), with scores ranging from 10 to 50. Higher scores indicate a higher possibility that participants suffer from a mental disorder.

The SBQ-R is a brief, 4-item self-report measure of past suicidal behavior. The questionnaire is used with adolescents between the ages of 13 and 18. Each question is rated on its own scale, with specific point values assigned to the answers and the total score ranging from 3 to 18 points. A higher score indicates a greater likelihood of engaging in suicidal behavior.

The WHO-5 is a brief self-report assessment used to measure mental well-being during the past 2 weeks. It includes five items with positive wording, each rated on a 6-point Likert scale (0 = at no time, 5 = all of the time). The total raw score, which ranges from 0 to 25, is multiplied by 4 to generate the final score. A high score indicates a higher level of well-being.

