#### Primary outcome

3.5.2

The primary outcome, symptoms of depression and anxiety, will be measured by the HSCL-25 (36) at baseline (t1), at the end of the intervention (t2) and 12 weeks after the end of the intervention (t3) to determine the effectiveness of the intervention. The HSCL-25 is a 25-item self-report questionnaire, on which participants rate if physical, emotional, or psychological symptoms indicating depression, anxiety, and trauma have affected them over the past week. Answers are given on a 4-point Likert Scale (1 = not at all; 4 = extremely), and total scores can range from 25 to 100, with higher scores indicating greater levels of depression, anxiety and trauma, respectively.

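### The HSCL-25 entry cut-off of 1.75 lies below the lowest total score the protocol allows (25), so as written the symptom requirement excludes no one

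*Protocol article*

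**What the plan says.** The inclusion list in section 3.3 (Eligibility criteria) has two symptom criteria joined by an or. The first is at least "sub-clinical depressive symptoms assessed by the Hopkins Symptom Checklist-25 (HSCL-25); total score > 1.75". The second is a K10 total score above 20. The exclusion list adds "Suicidality assessed by the Suicide Behaviors Questionnaire-Revised (SBQ-R); total score > 6".

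Section 3.5.1 (Screening measures) confirms the role of the two symptom scales: "inclusion criteria including the HSCL-25 and the K10". It gives the K10 as a sum, "with scores ranging from 10 to 50", and the SBQ-R as a total from 3 to 18. It gives no scoring for the HSCL-25.

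The only HSCL-25 scoring in the article is in section 3.5.2 (Primary outcome). There the instrument has 25 items, each rated from 1 to 4, and the resulting scale is described as follows: "total scores can range from 25 to 100, with higher scores indicating greater levels of depression, anxiety and trauma". Table 1 lists the HSCL-25 at screening as well as at baseline, post-intervention and follow-up.

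**The concern.** The two sections use the same term, total score, for the same instrument, but the threshold in one lies outside the range given in the other. No third place reconciles them, for example by defining an item-mean score for screening.

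The cut-off decides who enters the trial. Applied literally, it is met by a respondent who answers not at all to every item. Through the or, the K10 criterion would then never be decisive. That conflicts with the abstract, which describes recruits with symptoms of anxiety and depression or high perceived stress, and with the criterion's own wording about at least sub-clinical symptoms. A participant who enters at a sum of 25 is also at the floor of the primary outcome and has no room to improve on it.

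**Working it through.** **Inputs.** Number of items: 25 (section 3.5.2). Item scores: 1 to 4 (section 3.5.2). Stated total range: 25 to 100 (section 3.5.2). HSCL-25 cut-off: above 1.75 (section 3.3). K10: range 10 to 50 (section 3.5.1), cut-off above 20 (section 3.3). SBQ-R: range 3 to 18 (section 3.5.1), cut-off above 6 (section 3.3).

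**Step 1: reproduce the stated range.** Minimum = 25 × 1 = 25. Maximum = 25 × 4 = 100. This matches section 3.5.2, so the total score there is the item sum.

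**Step 2: apply the cut-off to that sum.** The attainable totals are the integers 25 to 100, which is 100 − 25 + 1 = 76 values. The smallest, 25, exceeds 1.75. The number of totals that fail is 0 of 76.

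**Step 3: carry this through the or.** The symptom requirement is (HSCL-25 > 1.75) or (K10 > 20). The first part is always true, so the whole is always true whatever the K10 score.

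**Step 4: check whether the other cut-offs show the same fault.** K10 > 20 lies inside 10 to 50. SBQ-R > 6 lies inside 3 to 18. Both are called total scores and both work on the sum scales given. The mismatch is confined to the HSCL-25.

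**Step 5: find the scale that 1.75 fits.** Item mean = sum / 25, with range 25/25 = 1 to 100/25 = 4. The value 1.75 lies inside this range. With complete items it converts to 1.75 × 25 = 43.75. A sum of 43 gives 43/25 = 1.72 and fails. A sum of 44 gives 44/25 = 1.76 and passes. On this reading the sums 25 to 43, which are 43 − 25 + 1 = 19 values, fail the HSCL-25 part. This only converts the protocol's own number; it does not propose a threshold.

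**Step 6: see whose eligibility depends on the reading**, with all other criteria met.

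| HSCL-25 sum | K10 | 1.75 as sum (as written) | 1.75 as item mean |
|---|---|---|---|
| 44 to 100 | any | eligible | eligible |
| 25 to 43 | above 20 | eligible | eligible through K10 |
| 25 to 43 | 20 or below | eligible | not eligible |

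Only the last row changes. The article gives no joint distribution of HSCL-25 and K10 scores, so the share of screened adolescents in that row cannot be calculated.

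**The case against.** The strongest reply is that this is a mislabelled score. A cut-off with two decimals makes no sense against a sum that starts at 25, and the criterion is plainly meant to select people with symptoms. Screening staff would probably score an item mean, so recruitment may work as intended. This is plausible and cannot be ruled out. But nothing in the article confirms it: REDCap is named as the platform, and how it computes the screening score is not described. Nor is this a detail that a condensed article leaves to the full protocol, since two published statements conflict.

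The reply does rule out several stronger readings that a reader might infer.

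- *Every screened adolescent enters.* Not supported. Age, refugee status, language, consent, the SBQ-R exclusion, planned departure and concurrent skills training still restrict entry. Only the symptom requirement is lost.
- *The two readings differ for every HSCL-25 sum from 25 to 43.* Not supported. Those with K10 above 20 enter either way.
- *The trial effect will be diluted by a known amount.* Not supported. The size of the affected group is unknown, and the K10 route admits people with low HSCL-25 scores even under the item-mean reading.
- *The primary analysis is compromised by an undefined outcome scale.* Not supported. Section 3.5.2 states the outcome as a 25 to 100 total. With complete items, sum and mean differ only by a factor of 25, so tests and standardised effects are the same. The sample size in section 4.1 rests on f = 0.25 and is unaffected.

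**Conclusion.** The criterion is wrong as written. On the protocol's own scale, none of the 76 possible HSCL-25 totals fails it, and the K10 alternative becomes redundant. This follows from the document alone and needs no outside assumption.

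That 1.75 is an item mean is an inference. It rests on the value lying within 1 to 4 and being impossible as a 25 to 100 sum; the equivalent of 43.75 also assumes no missing items. If the inference is right, the practical difference is confined to adolescents with a sum of 25 to 43 and a K10 of 20 or below. If screening already uses the mean, no participant is affected and only the text needs correcting. The point deserves action because it concerns a decision threshold and is cheap to settle, not because harm to the trial has been shown.

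**What to change.** The sponsor should reconcile sections 3.3 and 3.5.2 by stating whether the existing cut-off refers to the item mean or to the sum, and by writing it on that scale under a matching name. If the score is a mean, the text should no longer call it a total. Which score was intended is for the sponsor to confirm.

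The sponsor should also verify that the REDCap screening field computes the score that the corrected criterion names. If the field applied 1.75 to the sum, participants already enrolled with a K10 of 20 or below should be identified, so that the report can describe the recruited population correctly.

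The primary outcome needs no change of scale. The cost is a one-line correction to the text and one check of a scoring field; sample size, analysis model and assessment schedule are untouched.
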